## Abstract

**Background:**

Adolescent idiopathic scoliosis (AIS) is one of the most prevalent spinal deformities that may progress sharply during growth. The aim of this study will be to evaluate the efficacy of three-dimensionally integrated exercise on the Cobb angle, angle of trunk rotation, sagittal profile, and quality of life in patients with AIS.

**Methods/design:**

The study is designed as a randomized controlled trial. Participants include 42 patients with AIS aged 10–16 years. Randomly assigned patients will follow a 6-month treatment, either in a control group with standard care of observation following the Scoliosis Research Society criteria or in an experimental group with three-dimensionally integrated exercise for scoliosis. Blinded assessments at baseline and immediately after intervention will include the change of Cobb angle, angle of trunk rotation, sagittal index, and quality of life.

**Discussion:**

If we find that the intervention is effective in improving Cobb angle, angle of trunk rotation, sagittal profile, and quality of life in patients with AIS, this trial will have a positive impact and warrant a change in clinical practice.

**Trial registration:**

ClinicalTrials.gov, NCT03427970. Registered on February 9, 2018, and revised on July 24, 2018.

**Electronic supplementary material:**

The online version of this article (10.1186/s13063-018-2834-x) contains supplementary material, which is available to authorized users.

## Background

Scoliosis is a three-dimensional deformity with lateral curvature, sagittal hypokyphosis, and axial rotation of the spine. Adolescent idiopathic scoliosis (AIS) with a Cobb angle greater than 10 degrees occurs in the general population with a frequency ranging from 2% to 5% during growth, and the origin of the disease is unknown [1–4]. It has been highlighted that impairment of esthetic appearance of a patient’s body is significantly related to the patient’s negative image and self-respect, and the disease may cause reduced bone strength and balance disorder, among other effects [5–7]. If uncontrolled, scoliosis can progress in a short time, and moreover, severe trunk deformity, cardiopulmonary impairment, and low quality of life may occur [1, 8]. There is still no intervention to cure scoliosis [1, 8].

According to the severity of the curve, the major treatment approaches for patients with AIS include exercises, bracing, and surgery to correct, prevent, or stop the progression of the deformity [1, 8, 9]. In North America, the Scoliosis Research Society (SRS) has published the standard of care for AIS: Patients with curvature between 10 degrees and 25 degrees who are still growing should be kept under observation [9]. In Europe, the International Scientific Society on Scoliosis Orthopaedic and Rehabilitation Treatment has recommended that physiotherapeutic scoliosis-specific exercises should be the first step in treating idiopathic scoliosis to prevent/limit the progression of the deformity [1, 8]. Three-dimensionally integrated exercise for scoliosis is based on the theory of physiotherapeutic scoliosis-specific exercises and consists of patient education, three-dimensional self-correction, stabilization of the corrected posture, and training activity of daily living, combined with neuromotor control, proprioceptive training, balance training, and so forth, tailoring the exercise approach individually for each patient [1, 8, 10]. The specific exercises could accelerate the recovery of physiology, psychology, and functional ability for patients with AIS as compared with other approaches, but these outcomes may take a long time to achieve [11–19].

The Cobb method is the gold standard for measuring the scoliotic curve clinically [20], and the trunk rotation and sagittal profile are also used to assess the trunk deformity and the physiological curvature for patients with spinal diseases [21–23]. Normally, different interventions will achieve varied satisfaction levels related to treatment and quality of life for patients [24]. Limited evidence from 3-month studies of three-dimensionally integrated exercise for scoliosis have confirmed its positive value in preventing the curve progression, maintaining the corrected posture, and improving patients’ quality of life [25, 26]. However, better-quality research needs to be conducted before the use of three-dimensionally integrated exercise for scoliosis can be recommended in clinical practice. Therefore, the objective of this trial is to determine the effect of intervention on the Cobb angle, angle of trunk rotation (ATR), sagittal profile, and quality of life compared with standard care for patients with AIS.

## Methods/design

### Aims and objectives

The aim of this study is to assess the effect of the intervention on Cobb angle, ATR, sagittal profile, and quality of life in patients with AIS.

### Study design

The present study is a randomized controlled trial (RCT) comparing a 6-month three-dimensionally integrated exercise for scoliosis intervention with a standard of care of observation alone (control group). The protocol conforms to Consolidated Standards of Reporting Trials (CONSORT) guidelines for nonpharmacological studies [27, 28] and the World Health Organization Trial Registration Data Set Version 1.2.1 guidelines for clinical trials protocols (See in Table 1 and Additional file 1). The study is being conducted at the Department of Rehabilitation Medicine, Xinhua Hospital affiliated to Shanghai Jiao Tong University School of Medicine, China. A trained research assistant who is blinded to the randomization design will invite eligible patients to attend the specific scoliosis clinic to participate in the study. The physician in the clinic will explain the whole protocol in the quiet clinic room and obtain written informed consent from each participant and legal representative prior to inclusion. The trial profile is displayed in Fig. 1.

**Table 1 Tab1:** World Health Organization Trial Registration Data Set (Version 1.2.1)

Item number	Item	Description	Addressed on page number
1	Primary registry and trial identifying number	Name of primary registry and the unique identifier assigned by the primary registry	3
2	Date of registration in primary registry	Date when the trial was officially registered in the primary registry	3
3	Secondary identifying numbers	Other identifiers, if any Universal Trial Number Identifiers assigned by the sponsor Other trial registration numbers issued by other registries Identifiers issued by funding bodies, collaborative research groups, regulatory authorities, ethics committees/institutional review boards, etc.	Not applicable
4	Sources of monetary or material support	Major sources of monetary or material support for the trial (for example, funding agency, foundation, company, and institution)	17
5	Primary sponsor	Person, organization, group, or other legal entity that takes responsibility for initiating and managing a study	17
6	Secondary sponsor(s)	Additional persons, organizations, or other legal persons, if any, who have agreed with the primary sponsor to take on responsibilities of sponsorship	Not applicable
7	Contact for public queries	E-mail address, telephone number, and postal address of the contact who will respond to general queries, including information about current recruitment status	2
8	Contact for scientific queries	Name and title, e-mail address, telephone number, postal address, and affiliation of the principal investigator and e-mail address, telephone number, postal address, and affiliation of the contact for scientific queries about the trial (if applicable)	2
9	Public title	Title intended for the lay public in easily understood language	1
10	Scientific title	Scientific title of the study as it appears in the protocol submitted for funding and ethical review; include trial acronym, if available	Not applicable
11	Countries of recruitment	Countries of recruitment Countries from which participants will be recruited	5
12	Health condition(s) or problem(s) studied	Primary health condition(s) or problem(s) studied (for example, depression, breast cancer, or medication error)	4
13	Intervention(s)	For each group of the trial, record a brief intervention name plus an intervention description name. For drugs, use the generic name; for other types of interventions, provide a brief descriptive name of the intervention. This name must be sufficiently detailed for it to be possible to distinguish between the groups of a study; for example, interventions involving drugs may include dosage form, dosage, frequency, and duration	5–10
14	Key inclusion and exclusion criteria	Inclusion and exclusion criteria for participant selection, including age and sex	7–8
15	Study type	Method of allocation (randomized/nonrandomized) and blinding/masking (identify who is blinded) Assignment (for example, single-group, parallel, crossover, or factorial) and purpose Phase (if applicable) For randomized trials, method of sequence generation and allocation concealment	5
16	Date of first enrollment	Anticipated or actual date of enrollment of the first participant	16
17	Target sample size	Total number of participants to enroll	13
18	Recruitment status	Pending: Participants are not yet being recruited or enrolled at any site Recruiting: Participants are currently being recruited and enrolled Suspended: Temporary halt in recruitment and enrollment Complete: Participants are no longer being recruited or enrolled Other	16
19	Primary outcome(s)	The primary outcome should be the outcome used in sample size calculations or the main outcome used to determine the effects of the intervention For each primary outcome, provide the following: Name of the outcome (do not use abbreviations) Metric or method of measurement used (be as specific as possible) Time point of primary interest	10
20	Key secondary outcome(s)	As for primary outcomes, for each secondary outcome, provide the following: Name of the outcome (do not use abbreviations) Metric or method of measurement used (be as specific as possible) Time point of interest	10–12

**Fig. 1 Fig1:**
[figure not shown]
Trial profile

### Participants

#### Inclusion criteria

A diagnosis of AIS [8]Aged 10 to 16 yearsA Cobb angle of 10–20 degreesA Risser sign of 0–3No other treatment that might affect scoliosis

#### Exclusion criteria

Nonidiopathic scoliosis, which is caused by neuromuscular disorder, vertebral malformation, trauma, tumor, or other diseasesAccompanying psychiatric problems or neuromuscular or rheumatic diseasesPrevious surgical history involving the spine or lower extremitiesPrevious exercise or brace treatment historyHaving contraindications to exercise

### Randomization and masking

After an initial assessment examination confirming eligibility and collection of baseline data, participants will be allocated by a physician using computer-generated block randomization in a ratio of 1:1 to the experimental group or control group. The allocations will be concealed in sequentially numbered, opaque, sealed envelopes with a signature across the sealing point.

Because of the nature of the intervention, physical therapists and patients cannot be blinded when offering or receiving the treatment. However, patients will be asked not to reveal their group allocation to ensure blinding of the evaluator. To minimize bias, strict eligibility will be maintained in the whole trial, and there are separate rooms for assessment and treatment, so that each group will hardly know much about each other. A trained evaluator blinded to group allocation will complete all patient assessments at baseline and immediately after the 6-month intervention. Both groups will continue with their routine activities, but they will not be able to attend any other formal exercise program. The statistician will not be aware of the data coding. Figure 2 illustrates the timing of all trial processes (Additional file 2).

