### Assessment

The following demographic data and patient characteristics of the experimental group will be collected: age, gender, height, weight, body mass index, Risser sign, time since menarche for female patients, curve pattern, apex levels, and exercise compliance. Skeletal immaturity based on the Risser stages will be recorded for each patient at the first assessment. Curvatures will be classified according to the Ponseti classification system, which distinguishes four major types of scoliosis: thoracic, lumbar, thoracolumbar, and S-shaped [8, 33]. Development of the ossification of the iliac crest is used to assess the remaining spinal growth, and the stage of ossification of the iliac apophysis can be seen on a radiograph. The Risser sign is an assessment of skeletal maturity and spinal growth. It is based on the ossification of the iliac apophysis, which is evaluated with a four-grade scale from 0 (no ossification) to 5 (fused ossified apophysis) [34]. The outcome measures described in the subsections that follow will be performed before and after 6 months of intervention in both groups.

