### Data collection, data management, and statistical analysis plan

The primary outcome is the change of Cobb angle, and the secondary outcome measures will include the ATR, sagittal index, and quality of life. Descriptive statistics will be calculated for baseline demographics, physical examination, radiographs, and questionnaire data, and results will be presented as the mean ± SD, whereas categorical variables will be expressed as percentages. The chi-squared test will be used to compare the categorical/dichotomous variables. Separate analyses will be conducted for each outcome.

Data will be entered using EpiData software designed for this study. All data will be collected, typed, and analyzed by a masked statistician who will not have access to study assignment. The main investigators will check the data every 2 weeks to ensure the quality.

The primary endpoint is the pre- and posttreatment difference in the Cobb angle. We have calculated that a sample size of 21 patients per group would be capable of detecting a between-group difference of 5 degrees in the primary endpoint with a type I error of 5% and a power of 95% [20]. Because the interval of Cobb angles at entry is 10–20 degrees, and assuming a uniform distribution of Cobb angles in this range (the most unfavorable scenario), an SD of 5 degrees is estimated [8].

Baseline comparability will be assessed using Student’s *t* test for independent samples. To screen for variables associated with each of the outcome variables, univariate linear mixed models for each relevant covariable (age, gender, body mass index, Risser sign, time since menarche, apex levels, curve pattern, and compliance may have associations with risk of progression) will be conducted.

Multiple linear mixed models for each time point will be tested, including covariables found significant at *p* ≤ 0.20 in the univariate analysis, and after screening for multicollinearity [42].

For the ordinal outcome (SRS-22, which is based on only one item with five levels), generalized linear mixed effects model analysis will be used.

Furthermore, because subjects with younger than 13 years of age are characterized by a higher risk of progression [43], the patients will be divided into two subgroups (age < 13 years and age ≥ 13 years), and a linear mixed model analysis for the primary outcome will be performed on each subgroup.

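### The primary comparison of change in Cobb angle does not guarantee adjustment for entry Cobb angle or age: entry Cobb is absent from the covariable list, and age stays only if it passes a p ≤ 0.20 screen.

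*Protocol article*

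**What the plan says.** Under Randomization and masking, the protocol article states that "participants will be allocated by a physician using computer-generated block randomization in a ratio of 1:1 to the experimental group or control group". No stratification or minimisation factor is named. The Inclusion criteria admit ages 10 to 16 and Cobb angles of 10 to 20 degrees.

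The section Data collection, data management, and statistical analysis plan fixes four things that matter here:

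- The endpoint: "The primary endpoint is the pre- and posttreatment difference in the Cobb angle". Under Assessment, the outcomes are measured at two points only: "The outcome measures described in the subsections that follow will be performed before and after 6 months of intervention in both groups".
- The candidate covariables: "age, gender, body mass index, Risser sign, time since menarche, apex levels, curve pattern, and compliance may have associations with risk of progression". Entry Cobb angle is not among the eight.
- The rule for keeping them: the multiple models are fitted "including covariables found significant at *p* ≤ 0.20 in the univariate analysis", after a check for multicollinearity.
- A statement on prognosis: separate primary-outcome models are planned below and from 13 years, "because subjects with younger than 13 years of age are characterized by a higher risk of progression".

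**The concern.** The baseline value of the outcome is usually the first covariate considered for a continuous endpoint, and here an otherwise explicit list leaves it out. A change score subtracts the entry angle but does not remove its influence if the entry angle predicts the change. Regression to the mean is one way that could happen: entry is limited to a 10-degree window, and Suspension criteria treats 5 degrees as the reliability of the radiographic measurement.

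For age, the protocol itself names a boundary with a higher risk of progression on one side. Adjustment for it nevertheless depends on a significance screen in about 40 patients. A factor already judged prognostic can fail such a screen for lack of power.

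At stake are the precision of the primary estimate and how readily it can be interpreted if the arms turn out to differ in entry angle or age.

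**Working it through.** **1. The plan's own figures.** Sample measurement gives changes of −1.55 ± 4.39 and 2.90 ± 2.60 degrees, α 0.05 and β 0.05.
- Difference: 2.90 + 1.55 = 4.45 degrees.
- Pooled SD: √((4.39² + 2.60²)/2) = 3.61. Standardised effect: 4.45/3.61 = 1.23.
- A two-sided t test (sidedness assumed) at 95% power needs 19 per group (power 0.959), and 19 × 1.10 = 20.9, so 21.

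The stated 19 and 21 are reproduced. The sample size is not in question here.

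**2. Chance imbalance in age.** The share under 13 is not given, so 14 to 21 of 42 is assumed. With 21 per arm, the number under 13 in one arm is hypergeometric. The probability that the arms differ by 4 or more is:

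| Under 13, of 42 | Probability |
|---|---|
| 14 | 0.33 |
| 15 | 0.20 |
| 18 | 0.35 |
| 21 | 0.22 |

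With an odd total the difference is odd, so 4 or more means 5 or more; this is why the figures alternate. The range is 0.20 to 0.35.

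**3. Chance imbalance in entry Cobb.** The standard error of the difference in means is SD × √(2/21) = SD × 0.309.
- A uniform distribution on 10 to 20 has SD 10/√12 = 2.89. SE = 0.89, and the probability of a difference of at least 1 degree is 0.26.
- With the SD of 5 stated in the analysis section, SE = 1.54 and the probability is 0.52.

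**4. What an imbalance does to an unadjusted estimate.** Let r be the correlation of the covariate with the change. The documents do not give it; 0.2 to 0.5 is assumed. An imbalance of 0.5 SD or more has probability 0.105 for any one continuous factor. At 0.5 SD the shift is r × 3.61 × 0.5:
- r = 0.2: 0.36 degrees, 8% of 4.45
- r = 0.3: 0.54 degrees, 12%
- r = 0.5: 0.90 degrees, 20%

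In 40,000 simulated null trials per setting, with 21 per arm, overall type I error of the unadjusted test stayed at about 0.05. Among trials with an imbalance of at least 0.5 SD, it was 0.080 (r = 0.3) and 0.142 (r = 0.5), against about 0.05 with covariate adjustment.

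**5. How often the screen drops age.** By Fisher's z with 38 patients, age is kept when |z| × √35 exceeds 1.282.
- r = 0.2: 0.203 × 5.92 = 1.20, so age is dropped about 53% of the time.
- r = 0.3: 0.310 × 5.92 = 1.83, so it is dropped about 29% of the time.

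**6. Precision gained by adjusting for entry Cobb.** Let ρ be the correlation of baseline with follow-up, and σ a common SD. The change score has variance 2σ²(1 − ρ), and the adjusted analysis has residual variance σ²(1 − ρ²). The ratio is (1 + ρ)/2: 0.75 at ρ = 0.5 and 0.85 at ρ = 0.7.

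Equal SDs are an assumption. Entry is truncated to 10 to 20 degrees and follow-up is not. In general, with slope b of follow-up on baseline, the ratio is 1 − (b − 1)² × (baseline variance)/(variance of change). At b = 1 it is 1.00, which is no gain.

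In terms of r from step 4, adjustment multiplies the residual variance by 1 − r². Power at 19 per group then goes from 0.959 to 0.965 (r = 0.2) or 0.990 (r = 0.5).

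**The case against.** The strongest reply is that nothing is broken. Chance imbalance under valid randomisation causes no bias on average, and step 4 confirms that overall type I error stays at 0.05. A reader might infer that the missing strata distort the trial. The documents do not support that: any shift depends on the allocation obtained and on a correlation they do not report. Planned power is also already high. All of this stands, and it limits the weight of the point.

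A second reply is that age is already handled: it is a candidate covariable, it defines the subgroup models, and baseline comparability will be tested. This stands in part. The subgroup models do not adjust the overall comparison, and a baseline test adjusts nothing. Screening on association with outcome is not illogical in itself, since imbalance in a factor unrelated to outcome does no harm. The weakness is that a factor declared prognostic in advance is left to a low-powered test.

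A third reply is that the mixed models may take baseline and 6-month Cobb as repeated responses, in which case entry Cobb would not appear as a covariable. The wording leaves this open. With two visits and complete data, such a model reproduces the change-score comparison unless the arms are constrained to a common baseline mean, so it would not settle the matter by itself.

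It is also tempting to say that allocation should have been stratified by age because age is the only risk factor named. The protocol lists eight variables with a possible link to progression; age under 13 is merely the one with a cut-off. A trial of 42 cannot stratify on all of them, and a condensed article may leave strata to the full protocol. Recruitment began in February 2018, so a change now could not undo imbalance already present. Stratification is therefore optional and not part of this point.

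**Conclusion.** The point holds as a modest weakness in the stated analysis. The covariable list omits the baseline of the primary outcome, and adjustment for age is left to the data. Chance differences of a size worth adjusting for are common in 42 patients: probability 0.20 to 0.35 for 4 or more patients under 13, and 0.26 to 0.52 for 1 degree of mean entry Cobb. At an imbalance of 0.5 SD, an unadjusted estimate would move by 8 to 20% of the planned difference.

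These figures rest on an assumed share under 13, on an entry SD of 2.89 or 5, and on assumed correlations of 0.2 to 0.5 with the change. The precision gain from adjusting for entry Cobb runs from none to a variance ratio of about 0.75 over the cases shown. The conclusion does not depend on what a fuller document says about strata, because the list and the screen are in the current text.

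**What to change.** State in the analysis section that the primary model for Cobb angle includes baseline Cobb angle and age (continuous, or as under 13 versus 13 and over) as pre-specified fixed covariates, whatever the result of the p ≤ 0.20 screen. If Cobb angle is modelled as a repeated response, say how the baseline is handled, for example with a baseline mean common to both arms.

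Both variables are already collected. The cost is one sentence and two model degrees of freedom: 42 − 2 = 40 residual degrees of freedom become 38, or 36 become 34 at 19 per group. No patients are added, and patients already randomised are covered. The wording should be settled before any outcome data are examined by arm, including at the interim analysis.

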### Suspension criteria

In the interim analysis, clinical significance is defined as a 5-degree Cobb angle change, which is the reliability of radiographic examination and the international “gold standard” for minimally significant clinical change [31]. Decreasing or remaining in Cobb angle of 5 degrees means the treatment is successful, whereas increasing the Cobb angle to greater than 5 degrees is defined as failure of treatment [32]. There are no standard stopping criteria for specific exercise therapy outcome. Previous studies showed that there is a 40% failure rate for standard care (observation) [18]. In light of the clinical practice as well as the previous studies, the stopping criteria used in this protocol are as follows:If more than 40% of patients fail in either the experimental group with three-dimensionally integrated exercise for scoliosis or the control group, the trial will be ended, suggesting a change of treatment.During the whole study period, if the patient has significantly abnormal progression in clinical examination and the Cobb angle has reached ≥ 25 degrees, the patient (in either the experimental group or the control group) will be suspended from the study.

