#### SRS-22 dimension scores

The 22-item Scoliosis Research Society Outcomes Questionnaire (SRS-22) is especially designed for patients with idiopathic scoliosis [24]. The questionnaire consists of 22 items with 5 dimensions: function/activity, pain, self-image, mental health, and satisfaction with treatment. Each domain has five items each, except the satisfaction with treatment domain, which has only two items. The two satisfaction items are not included in the final analysis. Each item is scored from 1 (worst) to 5 (best). Results are presented as the mean of each scale (sum of 5 questions/5) and the mean subtotal score (sum of 20 questions/20) [39, 40]. In this study, we will use the validated Chinese version of SRS-22 [41].

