## Discussion

This study protocol describes an RCT that is designed to evaluate the efficacy of three-dimensionally integrated exercise on scoliosis measured as Cobb angle, the ATR in degrees, sagittal profile, and quality of life in patients with mild AIS.

In this study, the patients and intervention team are not blinded, because the intervention team needs to carry out the detailed treatment plan with the patients, and the patients in each group know their treatment plan. The assessor, enrollment assistant, and statisticians are blinded with respect to the patients’ treatment allocation. Meanwhile, there are separate rooms for assessment and treatment to avoid having other patients know about the treatment. The control group only needs to perform the assessment at the baseline and after the 6-month intervention, so they will have less time to communicate with the other patients. Once the patient asks to change the treatment plan, they will be eliminated from the study immediately.

Preventing the curve progression is the most important reason for treatment. There is still no intervention to cure AIS [1, 8]. The results of this RCT will provide valuable information for the family, patient, clinicians, and clinical decision makers, as well as to administrative stakeholders, and they may play an important role in providing healthcare services.

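### As described, the blind on the primary Cobb reading depends on unblinded patients not disclosing their arm, although a radiograph can be read without meeting them

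*Protocol article*

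**What the plan says.** All references are to the Protocol article.

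- **Who is unblinded.** Randomization and masking: "physical therapists and patients cannot be blinded when offering or receiving the treatment". The inclusion criteria set the age range at 10 to 16 years.
- **Who assesses.** The same section: "A trained evaluator blinded to group allocation will complete all patient assessments at baseline and immediately after the 6-month intervention". The Abstract (Methods/design) says: "Blinded assessments at baseline and immediately after intervention will include the change of Cobb angle", and lists trunk rotation, sagittal index and quality of life alongside it.
- **How the blind is kept.** Randomization and masking: "patients will be asked not to reveal their group allocation to ensure blinding of the evaluator". Separate rooms are also mentioned, with the reason that "there are separate rooms for assessment and treatment, so that each group will hardly know much about each other". The Discussion gives the same kind of reason: "there are separate rooms for assessment and treatment to avoid having other patients know about the treatment". It repeats that the assessor is blinded and adds no further mechanism.
- **What each measure requires.** The angle of trunk rotation is taken with a Scoliometer on the patient in forward bend, and the sagittal index from plumb-line distances on the patient. The Cobb angle is measured on a standing frontal radiograph. For the SRS-22, which has a treatment-satisfaction domain, "The two satisfaction items are not included in the final analysis".

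**The concern.** The angle of trunk rotation and the plumb line cannot be measured without examining the patient, so for those outcomes some risk to the blind is unavoidable. The Cobb angle is different. It comes from a stored image, and its blind could be made independent of anything a patient says or shows. As described, the article does not use that advantage: it gives all assessments to one evaluator, and it protects that evaluator by a request to adolescents who have spent six months either exercising or being observed.

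If the evaluator learns the arm at the 6-month visit and the film is read with that knowledge, any tendency to read the two arms differently enters the only primary outcome directly. Random reading error mostly costs precision. A reading difference linked to the arm adds to the estimated effect and does not shrink as patients are added. It also could not be distinguished from a treatment effect afterwards.

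**Working it through.** **Step 1: the plan's own figure.** Inputs from Sample measurement: change −1.55 (SD 4.39) in the experimental group and 2.90 (SD 2.60) in the control group, α = 0.05, β = 0.05.

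- Difference: 2.90 − (−1.55) = 4.45 degrees.
- Pooled SD: √((4.39² + 2.60²)/2) = 3.61 degrees.
- Standardised difference: 4.45/3.61 = 1.233.
- A two-sided two-sample t test at 95% power needs 18.10, so 19 per group. This matches the article; a one-sided test would need 15.
- Attrition: 19 × 1.1 = 20.9, so 21 per group, also as stated.

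The illustration below therefore uses the two-sided test, 19 analysed per arm and SD 3.61. It is repeated with SD 5, the value in the statistical analysis section.

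**Step 2: which safeguard protects what.**

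| Stated measure | Stated purpose | Protects the Cobb reading if a patient discloses? |
|---|---|---|
| Patients asked not to reveal their arm | Evaluator's blind | No; this is the measure that would have failed |
| Separate assessment and treatment rooms | Patients not learning about each other's treatment | No |
| Assessor described as blinded | A status, not a mechanism | No |

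**Step 3: what a leak could do.** Suppose there is no true effect and the 6-month readings differ between arms by a mean shift b because of knowledge of the arm. The t statistic then has noncentrality b/(SD × √(2/19)) on 36 degrees of freedom, with critical value 2.028.

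- SD 3.61: standard error 3.61 × 0.3244 = 1.17 degrees. The smallest significant difference is 2.028 × 1.17 = 2.37 degrees.
- SD 5: standard error 5 × 0.3244 = 1.62 degrees.

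| Mean shift b (assumed) | Noncentrality, SD 3.61 | Error rate, SD 3.61 | Noncentrality, SD 5 | Error rate, SD 5 |
|---|---|---|---|---|
| 0 | 0 | 5.0% | 0 | 5.0% |
| 0.5 degrees | 0.43 | 7.0% | 0.31 | 6.0% |
| 1 degree | 0.85 | 13.2% | 0.62 | 9.2% |
| 2 degrees | 1.71 | 38.3% | 1.23 | 22.4% |

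With all 21 per arm analysed, the rates at 0.5, 1 and 2 degrees are 7.2%, 14.2% and 41.8% (SD 3.61), or 6.2%, 9.7% and 24.4% (SD 5).

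**Step 4: from leak rate to mean shift.** The mean shift is the proportion of patients whose arm is known times the reading difference in those patients. With an assumed 2-degree difference in leaked cases, leakage in a quarter of patients gives 0.25 × 2 = 0.5 degrees, in half 0.5 × 2 = 1 degree, and in all of them 2 degrees. The lower rows of the table in Step 3 therefore describe widespread leakage with consistent reading differences.

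**The case against.** The strongest reply is that the article does specify a blinded assessor, tells patients not to disclose, separates the rooms and, being a condensed account, may leave film handling to a full protocol or manual. Much of this stands. No sentence names the person who reads the radiograph; that it is the evaluator is inferred from the assignment of all assessments together with the Abstract's list. Baseline data are collected before allocation, so a baseline reading made at that time cannot be influenced by arm, and only the 6-month reading is exposed. What remains is that the article does state how the evaluator's blind is kept, and the stated way is weak. The point concerns that mechanism, not a missing detail.

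Three stronger readings are tempting and are not supported:

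- **Film order.** A reader might infer from the Confidentiality section, where patients are identified partly by evaluation date, that the evaluator knows which film is baseline. That section is about identifying patients in the data. It does not say that films carry visible dates or are read in order. Knowing the time point without the arm would also shift both arms alike.
- **The questionnaire.** A reader might suppose that patients answer the satisfaction items in front of the evaluator. The article does not describe how the SRS-22 is administered, nor whether the two unanalysed items are completed. The statistical analysis section says that a masked statistician collects the data.
- **Reliability.** The Suspension criteria say that "clinical significance is defined as a 5-degree Cobb angle change, which is the reliability of radiographic examination", and a reader might set this against the planned 4.45 degrees as if the effect lay within reading error. The first figure concerns an individual change and the second a difference between group means. Random reading error averages out over the arm, so the comparison says nothing about bias.

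**Conclusion.** The point holds in a limited form. As described, the blind on the primary endpoint depends on the discretion of unblinded patients, although it need not. This is a weakness in the stated mechanism; it does not show that the blind fails, that the evaluator favours either arm, or that the trial's result would be wrong.

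The size depends on quantities that the documents do not give. Modest leakage, equivalent to a 0.5-degree mean shift, moves the 5% error rate only to about 6–7%. A 1-degree shift moves it to about 9–13%, and a 2-degree shift to about 22–38%. The figures rest on no true effect, 19 analysed per arm, a two-sided t test in place of the planned mixed model, and SDs of 5 and 3.61 degrees for the lower and upper ends of each range. Because the remedy costs so little, the change is worth making even if leakage is thought unlikely.

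**What to change.** State in Randomization and masking, and under the primary outcome, that the endpoint Cobb angle is measured as follows:

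- The same evaluator measures it from coded films on which identity, trial number and date are masked.
- Baseline and 6-month films are shuffled, read in batches and read away from the clinic visit, so that no reading follows directly on meeting the patient.

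For the visit itself, state that trunk rotation and plumb line are measured first, and that the patient then completes the SRS-22 alone and seals it. This is a precaution, since the article does not say how the form is handled at present.

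The cost is masking and shuffling about 84 films (42 patients × 2) and re-ordering the visit. No extra patients, procedures or readers are needed, and the sample size does not change. The one drawback is that the endpoint reading becomes separate from the eligibility and safety readings made at the visit, so the two must be recorded as distinct values. Films are stored, so those already taken can be masked and read this way as well.
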